
## Objectives

The main goal of this project is to address several gaps in the current literature in an exploratory way. This project seeks to have a meaningful impact on three fields of research:

The digital implementation of principles and approaches of ST into unguided self-help growth paths.The training of paraprofessional mental health service providers with listener training.The utilisation of paraprofessional mental health service providers in the delivery of online guided self-help interventions.

### Research questions

This study aims to address the following research questions:

Are OSIs based on ST approaches and principles feasible?Are OSIs based on ST approaches and principles efficacious (as compared to a waitlist), indicated by mental-health-related outcomes of participants?Is training of paraprofessionals in guiding the use of ST approaches feasible, and does such training improve their own mental health-related outcomes (as compared to a waitlist)?

Additionally, we seek to generate exploratory data on the following question using qualitative exploration:

How does the guidance by paraprofessionals trained in ST-informed approaches and principles affect the experience and outcomes of participants doing the ST-informed OSI?

## Methods and design

### Overview of research project and study design

The main components of our study are:

i)An exploratory, randomised, controlled trial following the definition of the National Institute for Health Research UK (NIHR UK) in a natural setting, pre-post-follow-up design with two parallel comparisons:
the 2 arm ST-informed OSI (growth path) intervention compared with a waitlist comparator condition among 7 Cups members, and,the 2-arm ST-informed paraprofessional provider/listener training compared with a waitlist comparator condition among 7 Cups listeners.

Each comparison uses a 1:1 allocation ratio. Figure 1 displays participant flow in each sub-study, including randomization to intervention vs. waitlist and subsequent follow-up assessments. Although this is not a fully powered randomized controlled trial (RCT), randomization will be used to test the procedure and to gather exploratory efficacy data.

**Fig. 1 Fig1:**
[figure not shown]
Outline of study design and flow of study participants

The design shall facilitate the examination of the exploratory primary and secondary research questions and was deemed practical for the naturalistic setting.

### Participants, interventions, and outcomes

#### Study setting

The study is conducted on the 7 Cups platform, an online community connecting people with emotional support features via a website (www.7Cups.com) and application. This platform is accessible to individuals worldwide, and data are collected from multiple countries eligible to use the 7 Cups platform.

#### Participant selection

Our study participants involve users on 7 Cups, with two types of users: members and listeners. These individuals may or may not have a diagnosed mental disorder, but they are not currently experiencing a crisis. Users seeking support, also called members, often face emotional and psychosocial distress. It’s important to note that 7 Cups is not intended to be used by anyone currently experiencing crises. Upon signup, users confirm they are not in crisis and agree not to use the platform for such situations. For crises, 7 Cups provides resources and alternative channels for help. Support on 7 Cups comes from trained paraprofessionals known as listeners. Paraprofessionals, referred to as listeners, provide support to the members or users of 7 Cups and are expected to be on the lower threshold of psychological distress compared to members.

#### Inclusion criteria

To be eligible for participation in our study requires being signed up on the 7 Cups platform as either a member or a listener. Members are defined as ​​individuals seeking support and looking to discuss their concerns. Listeners are paraprofessionals trained on the platform in active listening techniques to provide emotional support to members. For both members and listeners, the following eligibility criteria apply: (1) they have used the 7 Cups platform by logging in at least once in the last 2 weeks, (2) they are aged 18 years or above, (3) they agree to participate in our study and provide consent to data usage, and (4) they have sufficient English language proficiency to interact on the 7 Cups platform, participate in the intervention, and complete the assessments.

#### Exclusion criteria

Exclusion results from the refusal to consent to data use.

### Interventions

#### Structure of the ST-informed self-help (growth path) intervention

The growth path intervention is designed as a four-week, module-based program delivered on the 7 Cups platform. Participants can complete it at their own pace within approximately 4 weeks. The program comprises five modules with each taking approximately one week to complete except for the first module which is a brief onboarding module. Each week participants are introduced to ST principles and techniques [10, 11], namely joining, contracting, linework, witnessing, and sculpture work. Each module includes psychoeducational text, reflection prompts, and self-directed exercises. Joining focuses on the start of the process with particular emphasis on selecting and writing down a personal situation, with guidance on goal setting, non-judgmental attitudes, and motivation to participate. Contracting provides an informal contracting process that aims to foster commitment to complete the program within the 4-week timeline. Linework encourages the exploration of personal relationships through drawing exercises that encourage perspective taking in the context of a relevant salient situation and relationship, and as illustrated with lines and figures. Witnessing guides participants in imagining trusted relationships to observe their situation, interactions, and emotional responses from multiple perspectives. Sculpture work prompts participants to visualize and enact their situation with the use of physical objects, to explore relationship structures, and dynamics through guided acting exercises. The techniques are repeated with increasingly elaborate instructions. For example, with ‘’linework’’, start by drawing a circle that represents yourself, then draw a circle that represents your situation, then draw a line to represent the connection between the two circles. The intervention is standardised and monitored via proxy of the pre and post assessment completion dates, with reminders sent to participants that have not reached the end of the program as indicated by completing (or declining) the assessment.

#### Structure of the ST-Informed paraprofessional (Listener) training

The paraprofessional training intervention is closely aligned with the OSI content. It also consists of five modules and is designed as a four-week program. Each module introduces the same ST-informed principles and techniques, followed by additional guidance for paraprofessionals. These listeners are prompted to complete the reflective exercises themselves and then to consider how they might support members encountering similar activities. For example, in the ‘’witnessing’’ module, listeners practice perspective-taking in their own relationships and situations, reflect on what the experience would be like and where they can support a member, and subsequently learn to encourage members to reflect on different perspectives of a shared situation using the witnessing exercise. The intervention is standardised and monitored via proxy of the pre and post assessment completion dates, with reminders sent to participants that have not reached the end of the program as indicated by completing (or declining) the assessment.

#### Waitlist condition

Participants in the waitlist condition do not receive access to the ST-informed modules. They continue to use the general features of the 7 Cups platform (e.g., chat rooms, peer-support, standard listener responses, and forums) without receiving the specific ST-informed self-help or training material. To reduce contamination, active-condition participants are instructed not to share the material in any of the public or group spaces. These spaces are monitored and in any cases that links, exercises, or content is shared, the 7 Cups head of research (HOR) and their team removes them. Waitlist participants are granted full access to the ST-informed modules only after completion of the final (t2) assessment or upon withdrawal from the study (if they wish to access it after withdrawal).

Participants are sent reminders to encourage them to continue and complete the intervention and assessments every two weeks and the post assessment after 4 weeks. Adherence rates are measured and shall be included in the analysis as an indicator of the feasibility of the intervention. Participants in our study are free to use any concomitant support or interventions on the 7 Cups platform or elsewhere. Waitlist participants continue their usual use of 7 Cups, without any access to ST-informed intervention content during the waitlist phase. Waitlist participants are requested to report the use of any other growth paths on 7 Cups in the post assessment. Both conditions use 7 Cups as normal, but the active conditions have access to the ST-informed learning content that is not available elsewhere on the 7 Cups website.

#### Ancillary and post-trial support

We do not provide systematic ancillary and post-trial support, yet in case of such need, patients can direct themselves to multiple resources made available on the 7 Cups platform.

### Outcomes

Our outcomes are divided into primary and secondary outcomes. We provide a full list of assessment instruments in Table 1 which also includes the list of primary and secondary endpoints. The primary outcome of our study is the Kessler Psychological Distress Scale 6 (K6), which is a standardised self-reported outcome assessment tool used to measure global non-specific psychological distress with questions relating to depressive and anxiety symptoms. We selected the K6 for its brevity and validation in community-based samples ranging from subclinical to clinical distress [41, 42]. Although floor effects are a possibility in individuals without any significant distress, our preliminary assessments and data from 7 Cups suggest that a noteworthy proportion of participants have mild to moderate distress, making the K6 a pragmatic primary outcome measure. The primary endpoint of the study is the scores of the K6 assessment instrument, which consists of 6 items asking participants to rate their emotional states on a 5-point Likert scale ranging from ‘All the time’ to ‘None of the time’. The K6 is a widely used and accepted assessment instrument for measuring mental health-related intervention outcomes with confirmed reliability and validity. The K6 has good psychometric properties in the general population and is considered reliable with excellent internal consistency reliability of 0.89 [41, 42].

**Table 1 Tab1:** Measures and timepoints

Measure	Time point			References
	Pre	Post	Follow-Up (Post + 2 weeks)	
K6	x	x	x	Cornelius et al., 2013
PSS-4	x	x	x	Warttig et al., 2013
PHQ-4	x	x	x	Kroenke et al., 2003
UMUX-LITE		x*		Finstrad, 2010
MDMQ (4-item)	x	x	x	Steyer et al., 1997
Qualitative questions		x		
Sociodemo- graphic and other general information	x			

Abbreviations: K6, Kessler Psychological Distress Scale 6; PSS-4, Perceived Stress Scale-4; PHQ, Patient Health Questionnaire; UMUX-LITE, Usability Metric for User Experience; MDMQ, Multidimensional Mood State Questionnaire

*is not completed by subjects in waitlist condition

The secondary outcomes of the study are the Perceived Stress Scale 4 (PSS-4) [43], the 4-item Patient Health Questionnaire (PHQ-4) [44], the 2-item Generalised Anxiety Disorder Questionnaire (GAD-2) [44], and the Multidimensional Mood State Questionnaire (MDMQ, good-bad subscale) (English-language version of MDBF) [45]. Outcome data are collected through self-reported questionnaires and will be analysed to assess the effectiveness and feasibility of the intervention. In addition, a qualitative questionnaire is used to gather further information, feedback, and details about the experience and perceived quality of the intervention [46–48] (see Appendix A for a full list of qualitative and sociodemographic questions). Sociodemographic data are gathered during the baseline assessment for all participants and include age, gender, country of living, and level of education. Participants also complete questions to provide further details of any other interventions used during the intervention.

### Sample size

According to Bilingham et al., (2013) [49] sample size justification is very important, but power calculations may not be appropriate for feasibility studies. Following the recommendations of Gallinat et al., (2018) [50] and Leon, Davis and Kraemer (2011) [51], a sample size of 50 per group, considering potential attrition of 25%, is sufficient for feasibility studies. This sample size allows us to assess feasibility in online family, e-health, and mental health trials for recruitment capabilities, data collection and randomization procedures, participant flow, adherence, and acceptability [49–53] and is still sufficiently large to estimate rough variance for continuous outcomes and trends in expected direction and implementation of outcome measures [49]. We acknowledge that an exploratory study with a small sample size will need to be interpreted cautiously [51]. We thus aim to recruit *N* = 200 participants: 100 *members* (50 in the ST-informed online self-help condition and 50 in the waitlist) and 100 *listeners* (50 in the ST-informed paraprofessional training condition and 50 in the waitlist). Therefore, our targeted sample size of 200 participants should be viewed as supporting an *exploratory* aim. Future trials with a larger sample size will allow a more precise estimation of effect sizes.

### Recruitment

Recruitment for this study spans from 30-08-2023 to 31-03-2024 on the 7 Cups platform (extended from the original end date of 14-02-2024 due to lower-than-anticipated enrolment). During the recruitment period, a systematic process is adopted to enrol patients into the study. The complete informed consent is provided electronically before the beginning of the growth path, listener training or waitlist conditions without any deception. We recruit participants for the OSI/growth path intervention among those members who have signed up for the platform but are not registered or trained for ‘listener’ status. Participants for the paraprofessional/listener training intervention are recruited among those users who have registered as and trained for ‘listener’ status (i.e., volunteering as paraprofessionals on the platform to engage in synchronous text messaging with users seeking emotional support). We use advertisements to attract eligible users and listeners to participate in the study. All members and listeners are screened by the 7 Cups HOR according to the inclusion criteria described above. All members and listeners who are considered eligible are invited to participate in the study by the 7 Cups HOR through an announcement (Appendix B) with a full description of the study. Members and listeners need to provide informed consent to participate in the study (Appendix C) and complete a unique identifying code (UIC), which is a self-generated code that a participant generates by using the first two letters of their mother’s name, the day on which they were born, and the first two letters of the town/city in which they lived at the time of UIC generation (e.g., Mary, 02, Berlin; UIC = ma02be). Participants can withdraw from participation or request that their data be deleted by contacting the 7 Cups HOR.

### Methods, assignment of interventions

#### Allocation

The gold standard of double blinding is not applicable here due to the nature of the intervention, as participants inherently know which condition they are assigned to. Regarding the study team, there are two parts: one within 7 Cups (HOR) and one outside. The HOR team has access to participants, can allocate them, and send messages and links based on their assigned condition. The 7 Cups HOR compiles a list of all members and another list of all listeners who respond to the invitation, provide consent, and complete the UIC. These lists are securely stored on the 7 Cups server and only accessible to the 7 Cups HOR. The 7 Cups HOR provides these two lists of UICs, one for members and one for listeners, to the external team. The external team generates a randomization sequence using unique participant codes and passes this list to the HOR team. Thus, the external team has no immediate knowledge of allocation, and although the HOR team needs to know for procedural aspects, they are blinded to the randomization process. We utilise a random sequence generator to assign member and listener participants to the growth path or waitlist condition and the listener training or waitlist, respectively. The allocation sequence is generated using a computer-based tool provided by Sealed Envelope Ltd. This tool, titled “Create a blocked randomisation list,” was accessed online on August 29, 2023. The sequence was created with a seed of 21 for the list of members and seed of 23 for the list of listeners, and block sizes were set at 50, 100, 150, and 200, resulting in a total list size of 200 for members and 200 for listeners. This method reduces sequence predictability for the 7 Cups HOR who has direct contact with participants. The lists of assigned UICs are sent to the 7 Cups HOR, who messages participants links to either the growth path or waitlist assessments, and listener participants to either the listener training or waitlist assessments, as appropriate. Participants in the member and listener waitlist conditions do not receive any intervention until the waitlist assessments are completed. Upon completion of the assessments, waitlist participants are sent the links to the growth path or listener training for the waitlist members and listeners, respectively. A subsample of participant pairs is selected with each pair consisting of 1 listener and 1 member. The listeners have completed the ST-informed listener training and support their assigned member who is working through the OSI using the chat/messaging system on 7 Cups. For data analysis, the statistician is outside 7 Cups and unaware of allocation issues. The dataset includes allocation information for analysis, but the final data analysis will be performed on a coded dataset once data collection is complete. Regarding assessor bias, our assessments are conducted fully digitally and online without direct human involvement, eliminating the risk of assessor bias. For qualitative analysis, there may be a risk of bias if raters know about allocation. Therefore, we will have independent raters who are unaware of participants’ allocation. This approach is adopted to ensure the integrity and transparency of the study while acknowledging the limitations posed by the online setting.

### Data collection, management and analysis

The study employs a pre-post-follow-up design for the assessments. These assessments are facilitated through LimeSurvey, a General Data Protection Regulations (GDPR) compliant tool. The links for the t0 pre-assessment are sent to participants after being assigned to their respective conditions by the 7 Cups HOR. Our research team and the 7 Cups HOR monitor the progress of the participants and send them a link to complete the t1 post-assessment survey upon completion of the growth path, listener training, or 4 weeks into the waitlist condition. Participants who stop progressing on the growth path, listener training, or assessments for more than a week are sent reminders by the 7 Cups HOR. A link for the t2 follow-up assessment is sent two weeks after the completion of the t1 assessment. After completing the t2 assessment, the member and listener waitlist participants are sent the link to the growth path or listener training, respectively. If participants want to opt out of the study or request their assessment data to be deleted, they are instructed to contact the 7 Cups HOR or the Data Protection Officer at the IPU. After data cleaning, all participant UICs will be deleted, resulting in a fully anonymized dataset for further analysis.

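### The t0 baseline is collected after assignment, very probably from participants who know their arm, so it is open to arm-dependent reporting and non-response

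*Protocol article*

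**What the plan says.** The order of steps comes from two sections of the protocol article.

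- **Before randomisation.** Under Allocation, the platform's head of research (HOR) lists the users "who respond to the invitation, provide consent, and complete the UIC". Eligibility has been screened by then, but no outcome measure is described at this stage.
- **Randomisation and notification.** The external team randomises the codes and returns the assignments to the HOR, "who messages participants links to either the growth path or waitlist assessments". Listeners are handled in the same way.
- **Baseline.** Under Data collection, management and analysis: "The links for the t0 pre-assessment are sent to participants after being assigned to their respective conditions by the 7 Cups HOR".

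Allocation also says, in explaining why double blinding does not apply, that "participants inherently know which condition they are assigned to". Table 1 places the K6 (the primary outcome), PSS-4, PHQ-4 and MDMQ at the pre time point. The Outcomes section adds: "Sociodemographic data are gathered during the baseline assessment for all participants". The only measurement-bias safeguard stated for the questionnaires is that no human assessor is involved.

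**The concern.** In an open-label trial with self-reported outcomes, a baseline protects the comparison only if it is fixed before the participant can react to the allocation. Here t0 comes later, so two things can go wrong.

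1. **Reporting.** A participant told to wait may report more distress out of disappointment, and one given the programme may report less out of expectancy. The arms would then differ at t0 for a reason unrelated to the intervention, and any analysis that uses t0 as the reference point inherits that difference.
2. **Non-response.** A participant who leaves on learning the arm does so before any K6 or covariate is recorded. The Waitlist condition section makes an arm-dependent loss plausible: waitlist participants may have the modules after t2 or on withdrawing, so leaving early brings earlier access. The active arm has no such incentive.

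The trial asks whether the self-help programme is efficacious against waitlist, and its Discussion hypothesises larger reductions in distress in the intervention group. It also uses randomisation to test the procedure itself. Both purposes depend on a sound baseline.

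**Working it through.** **The plan's own figure.** Two comparisons with two arms each: "Each comparison uses a 1:1 allocation ratio". The Sample size section takes "a sample size of 50 per group, considering potential attrition of 25" per cent as sufficient. Four groups of 50 give 4 × 50 = 200, the stated target. If 50 is the number randomised, 50 × 0.75 = 37.5, or about 37 completers per arm. None of this is in dispute.

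**Scale for comparison.** The 95% margin for a difference between two arms, in SD units, is 1.96 × √(2/n):
- n = 50: ±0.39 SD
- n = 37: ±0.46 SD

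**Reporting shift at t0.** Let s be the amount, in SD, by which knowing the arm raises reported distress at t0 in the waitlist arm relative to the active arm. Let r be the correlation between t0 and t1, and assume equal SDs at both times. If the shift has gone by t1:
- change-score comparison: bias = s
- baseline-adjusted comparison: bias = r × s

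The article gives neither s nor r, so the values below are assumptions.

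| s (SD) | Change score | Adjusted, r = 0.6 | Adjusted, r = 0.5 to 0.7 |
|---|---|---|---|
| 0.1 | 0.10 | 0.06 | 0.05 to 0.07 |
| 0.2 | 0.20 | 0.12 | 0.10 to 0.14 |
| 0.3 | 0.30 | 0.18 | 0.15 to 0.21 |

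**Direction.** Disappointment raises waitlist distress at t0 and expectancy lowers active-arm distress at t0. Either one makes the waitlist arm appear to improve more, or the active arm less, than it did. Both understate benefit.

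**Dependence on the shift fading.** If a fraction p of the shift persists at t1, the understatement is (1 − p) × s for a change score and (r − p) × s with baseline adjustment. Complete fading (p = 0) therefore gives the largest change-score bias, and the adjusted result changes sign once p exceeds r.

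**Non-response at t0.** A difference of 10 to 20 percentage points means 0.10 × 50 = 5 to 0.20 × 50 = 10 more participants without t0 in one arm than in the other. As an upper bound, suppose that a fraction f of one arm is lost, that all of them come from one extreme of a normal K6 distribution, and that the other arm loses nobody. The observed baseline mean of the first arm then moves by φ(z)/(1 − f), where φ is the standard normal density and z its (1 − f) quantile:
- f = 0.05: 0.11 SD
- f = 0.10: 0.20 SD
- f = 0.20: 0.35 SD

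Real losses would be less extreme, and their direction cannot be derived from the article.

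**The case against.** Several points on the other side are fair.

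- **Knowledge of the arm at t0 is inferred.** The article says that t0 links follow assignment. It does not say outright that participants have been told their arm when they answer, and the flow figure and the announcement and consent appendices are not available here. The inference is nevertheless strong: the links differ by arm, participants are said to know their condition, and no concealment step appears.
- **A reader might infer that those who leave contribute no data at all.** The text does not support that. Codes and arms are on the lists, the Data management section records dropout, reminders go to people who stall on assessments, and the t1 link is not stated to depend on a completed t0. What is missing for these people is baseline K6 and covariates. How they enter the analysis is a matter for an analysis plan that is not shown.
- **A reader might infer spurious efficacy.** Under both mechanisms named, a shift that fades works against the intervention.
- **The sizes are assumptions.** The Statistical methods section plans mixed models with demographic covariates and does not say how t0 K6 enters. The two formulas therefore bracket common choices and do not describe a stated analysis.
- **The trial is exploratory.** It is declared not fully powered, promises cautious interpretation, and has a sampling margin of about ±0.46 SD, wider than every assumed bias. This lowers the urgency. It does not remove the point, because bias adds to sampling error and the procedure is itself under test for a larger trial.

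**Conclusion.** The point holds as a procedural weakness that should be fixed. t0 is placed after assignment, and the text strongly indicates that participants know their arm by then. The baseline K6, secondary outcomes and covariates are thus open to arm-dependent reporting and non-response. On assumed shifts of 0.1 to 0.3 SD that fade by t1, the effect estimate is biased by 0.1 to 0.3 SD (change score) or 0.06 to 0.18 SD (baseline-adjusted, r = 0.6), towards understating benefit. On an assumed 10 to 20 point difference in t0 non-response, 5 to 10 more of 50 are lost in one arm than in the other. The article does not establish that either has happened, and these figures do not show that the trial's result is invalid.

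**What to change.** **Order of steps.** Send the t0 survey with consent and code generation. Pass to the external team only the codes with a completed t0, and disclose the arm after that. This re-orders online steps and leaves N = 200 unchanged. The small cost is that people who do not complete t0 are not randomised, so a few more consents may be needed.

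**Participants already enrolled.** The Recruitment section gives an end date of 31-03-2024, so the re-ordering may serve only the follow-on trial. If it were made during enrolment, the two cohorts would have different baseline procedures and would need to be identified in the analysis. For anyone enrolled under the present order:

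- keep all randomised participants in the denominators;
- tabulate t0 completion by arm in each comparison, before the codes are deleted after data cleaning as the data collection section foresees;
- add a sensitivity analysis of t1 and t2 K6 without t0 in the model. It removes the bias from a shifted baseline but not the selection, so it has to be read with the completion table.

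These additions cost only analysis time, apart from the deadline set by the deletion of the codes.

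### The protocol gives conflicting rules for the t1 survey; one ties K6 measurement and its timing to finishing the programme in the active arms only

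*Protocol article*

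**What the plan says.** The protocol article addresses the timing of the outcome surveys in four places.

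- **Data collection, management and analysis.** Participants get a link to "complete the t1 post-assessment survey upon completion of the growth path, listener training, or 4 weeks into the waitlist condition". Then: "A link for the t2 follow-up assessment is sent two weeks after the completion of the t1 assessment". For those who stall: "Participants who stop progressing on the growth path, listener training, or assessments for more than a week are sent reminders by the 7 Cups HOR". That sentence provides a reminder, and does not say that a stalled participant is sent the t1 link.
- **Waitlist condition.** "Participants are sent reminders to encourage them to continue and complete the intervention and assessments every two weeks and the post assessment after 4 weeks". The sentence names no arm.
- **Structure of the ST-informed self-help (growth path) intervention.** "Participants can complete it at their own pace within approximately 4 weeks". Monitoring relies on assessment dates, with "reminders sent to participants that have not reached the end of the program as indicated by completing (or declining) the assessment". The listener training section uses the same monitoring rule.
- **Outcomes, Table 1.** The third time point is defined relative to the post assessment ("Follow-Up (Post + 2 weeks"), not relative to randomisation.

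The primary outcome is the K6. Both randomised comparisons, members and listeners, are against a waitlist.

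**The concern.** Under the Data collection rule, whether and when an active participant is asked for the primary outcome depends on something that happens after randomisation, namely finishing the programme. On the waitlist it depends only on the date. Because t2 hangs on t1, any loss or shift at t1 carries over to t2.

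Two things are at stake. The first is who is measured: if people who do not finish are not sent t1, the active arm is represented by its completers while the waitlist is represented by everyone who responds. The second is when: distress can change with time alone, so surveys at different intervals since randomisation mix that change with the intervention effect.

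Calling the trial exploratory excuses wide intervals. It does not excuse a difference between arms in how the outcome is obtained, because the estimates are meant to inform larger trials. When the links go out is also a matter of conduct that this document states itself; it is not something left to an analysis plan.

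**Working it through.** The protocol states no figure on this point, so there is none to reproduce. The check is a comparison of the rules, followed by an illustration of size.

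**Step 1. The rules side by side**

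| Question | Data collection section | Waitlist condition section | Intervention structure sections |
|---|---|---|---|
| t1, active arms | when the programme is completed | after 4 weeks, no arm named | assessment marks programme end |
| t1, waitlist | at 4 weeks | after 4 weeks | not addressed |
| t2 | two weeks after t1 is completed, all arms | not addressed | not addressed |
| Participant who does not finish | reminder after more than a week's stall | reminders every two weeks | reminders until the assessment is completed or declined |

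For the active-arm t1 there are two triggers, completion and 4 weeks. The third column adds a near-circularity: the survey signals that the programme has ended, while the Data collection section makes the end of the programme the signal to send the survey.

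**Step 2. Timing**

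Let T be the weeks an active participant takes to finish. Under the Data collection rule, t1 falls at about T in the active arm and about 4 on the waitlist, a difference of T − 4. With equal response delays, t2 falls at T + 2 and 4 + 2, so the same difference carries over. The programme is designed for about 4 weeks, so T − 4 is near zero for those who keep to plan. It is not fixed at zero, because the programme is self-paced.

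**Step 3. Who is measured**

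Let m be the share of the active arm with no t1, and g the difference in K6, in SD units, between completers and non-completers that baseline does not explain. The whole-arm mean is (1 − m) × completer mean + m × non-completer mean. Hence the completer mean differs from the whole-arm mean by m × g.

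Inputs:
- 50 per group and 25% attrition, from the Sample size section.
- m = 0.25 (equal to that attrition figure) and m = 0.50: assumed.
- g = 0.2 to 0.5 SD: assumed. The documents give no K6 SD, completion rate or completer gap.
- Waitlist fully measured, complete-case comparison: assumed, the least favourable case.

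SE = √(1/50 + 1/(50(1 − m))).

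| m | g (SD) | Bias m × g (SD) | SE (SD) | Two-sided error at nominal 5% |
|---|---|---|---|---|
| 0.25 | 0.2 | 0.05 | 0.216 | 5.6% |
| 0.25 | 0.3 | 0.075 | 0.216 | 6.4% |
| 0.25 | 0.5 | 0.125 | 0.216 | 8.9% |
| 0.50 | 0.2 | 0.10 | 0.245 | 6.9% |
| 0.50 | 0.3 | 0.15 | 0.245 | 9.4% |
| 0.50 | 0.5 | 0.25 | 0.245 | 17.5% |

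**Step 4. The other reading**

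If the post assessment goes to every arm at 4 weeks, the trigger itself leaves nobody out. The trigger-induced part of m is then zero, and only ordinary non-response remains.

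**The case against.** A reader might infer that active participants who do not finish are never measured. The documents do not support that. No sentence says so. The 4-week sentence in the Waitlist condition section mentions continuing the intervention, which only active participants can do at that stage, so it plausibly covers them despite the heading. The structure sections also prompt those who have not finished until they complete or decline the assessment. This part of the objection stands. It does not settle the matter, because the 4-week sentence is about reminders and may mean the link or only a prompt, and because it then contradicts the Data collection section.

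Other points on that side also stand:
- The dependence of t2 on t1 applies to the waitlist too, so a waitlist participant who skips t1 also gets no t2 link. It is not a filter in one arm only.
- Selection in both arms partly cancels. With shares m and gaps g in each arm, the bias is the difference of the two products, and it is zero if they are equal.
- The direction is not known. People who stop because they feel better would bias the contrast against the intervention.
- A likelihood-based mixed model using baseline K6 can be valid if missingness is explained by observed data. It is too strong to say that no model could help, although the condition cannot be tested.
- Nothing in the protocol suggests that finishing far from 4 weeks is typical.

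None of this removes the conflict between the rules.

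**Conclusion.** The point holds in a limited form. The protocol contains incompatible or unclear rules for sending t1 in the active arms. The more explicit one ties measurement of the K6, and its timing, to adherence in those arms only. If that rule was followed as written, the randomised comparison may become partly a completer comparison, at t1 and again at t2.

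Size and direction are unknown. The 0.05–0.25 SD in the table is an illustration that rests wholly on assumed completion shares and gaps, a fully measured waitlist and a complete-case comparison. It should not be read as an estimate, nor as evidence that the results will favour the intervention. Under the 4-week reading for all arms, it largely disappears. What is certain is that the text leaves open which of the two situations applies, and that this should be settled for the primary outcome.

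**What to change.** Reconcile the two intervention structure sections, the Waitlist condition section, Table 1 and the Data collection section to one rule: t1 is sent 4 weeks and t2 6 weeks after a common origin to every randomised participant in every arm, regardless of programme progress and, for t2, regardless of whether t1 was completed. Use one schedule of assessment reminders for all arms.

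The origin needs care, because the t0 link goes out after assignment. Either use randomisation and send t0 at once, or use the t0 date. Randomisation has the advantage that it is defined for everyone, including those who never answer t0. Table 1 would then give t2 as a time from the origin rather than from the post assessment.

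The cost is a change in when links are sent and a few sentences of text. The downside is small: some active participants are measured before they finish all modules, which is what a comparison of everyone randomised calls for.

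Recruitment and data collection were planned to end on 31-03-2024, so the schedule may no longer be changeable. For data already collected:
- state which t1 rule was applied in each arm;
- analyse all randomised participants;
- report t1 and t2 completion, and actual time since randomisation, by arm;
- add time since randomisation to the model as a sensitivity analysis.
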